### Statistical analysis – selecting patient management

A prediction rule is not a decision rule [39]. For physicians, it may be unclear how predictive information may be employed to change a patient's management beneficially. We would like to incorporate knowledge on treatment effects into our model(s) to guide physicians and patients in their decisions on how management should change given the predicted probabilities that a predictive model provides. In that respect, separate prediction of long-term outcomes for the sub domains of the CRQ may be much more unequivocal than a prediction of the total score in one or two years time. So, it is still attractive to explicitly model effects of treatment as to provide physician and patient with predictions conditional on particular treatments. Although the ICECOLD ERIC cohort(s) contain some information on treatment effects, we expect that the combined evidence from RCTs on COPD or good meta-analyses thereof may be a more fruitful source to see how predictions may be altered beneficially. This topic is currently being debated by our group and we cannot be more specific here.

### Sample size

The number of covariables that we will consider for the regression analysis is roughly 20, and using the rule that at least ten times as many patients are needed than covariables considered, we will need at least 200 patients per population.

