## Methods/Design

### Study design

We will conduct two prospective cohort studies (Swiss and Dutch counterparts), following a similar study protocol. We hope to be able to collect data from other cohort studies with similar protocols at a later stage. Figure 3 contains a flow chart of the study. The study has been approved of by all local ethic committees and is registered on the website  with the identifier: NCT00706602.

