### Outcomes

The primary outcome, for which the risk index will be developed, will be COPD-specific health-related quality of life as measured by the Chronic Respiratory Questionnaire (CRQ). COPD-specific health-related quality of life is one of the main outcomes used in prognostic COPD research whether observational or interventional [11-13]. Secondary outcomes will include COPD exacerbations requiring medical treatment and mortality.

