### Population

We will include patients ≥ 40 years of age with COPD in GOLD stage 2–4 (postbronchodilator FEV1/FVC ≤ 0.70 and postbronchodilator FEV1 ≤ 80% of predicted), who are able to complete the baseline assessment and who have been free of exacerbation for at least four weeks. Exclusion criteria will be a life expectancy of ≤ 12 months (predicted by the patient's GP), dementia, psychosis or other psychiatric morbidity that invalidates assessment of patient-reported parameters such as health-related quality of life, physical activity or dyspnea, and inability to complete the baseline assessment due to language difficulties. These criteria will be evaluated in cooperation with the participating GPs by browsing the patients' charts and during the eligibility testing.

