### Statistical analysis – prediction model

In choosing an approach to the statistical analysis, the use of the risk index in practice should be kept firmly in mind. The goal is prediction of the course of illness as expressed in health-related quality of life, risk of exacerbation and mortality. In principle, the CRQ has four domains (dyspnea, fatigue, emotional function, and mastery) and domain-specific predictions probably will trigger different therapeutic actions. So, potentially, seven different prediction models can be built: 4 on the CRQ domains, one for the overall CRQ score, one for exacerbation risk, and one for mortality, respectively. These models are likely to have at least some predictors in common. We envision that a practitioner will collect all predictors and receive a pattern of 7 predictions to discuss with the patient and base the therapy on. The added value of information whose collection requires more time (sit-to-stand test, questionnaires) will be systematically assessed. Obviously, the different endpoints require the use of different regression techniques: linear regression (CRQ), Cox regression for recurrent events (exacerbations) and Cox or logistic regression for mortality.

In clinical terms we envision the use of a prediction model in the following situations. First, in patients who visit the practice and are first diagnosed as having COPD. And second, in patients known to have COPD, who are identified through the electronic patient charts for a scheduled follow up visit. Our model will not be optimally suitable for use at unscheduled visits, triggered perhaps by exacerbations due to our exclusion criterion on current exacerbations.

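### The rule of ten patients per covariable supports the linear CRQ models only; for the planned mortality model the same ratio would need 200 deaths

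*Protocol article*

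**What the plan says.** The Sample size section is two linked statements. The first is the candidate count: "The number of covariables that we will consider for the regression analysis is roughly 20". The second is the rule and its result: "at least ten times as many patients are needed than covariables considered, we will need at least 200 patients per population". It treats the regression analysis as one thing and does not distinguish outcomes. It gives no expected number of deaths or exacerbations.

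There are two populations: "We will conduct two prospective cohort studies (Swiss and Dutch counterparts), following a similar study protocol". The minimum total is therefore 400.

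On outcomes, the Outcomes section says: "The primary outcome, for which the risk index will be developed, will be COPD-specific health-related quality of life". Exacerbations and mortality are secondary. The section Statistical analysis – prediction model foresees up to seven models: five for CRQ (four domains and the overall score), one for exacerbation risk and one for mortality. CRQ gets linear regression; the other two get "Cox regression for recurrent events (exacerbations) and Cox or logistic regression for mortality".

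The mortality model is more than a passing idea. The Abstract says that the best predictors of the outcomes, mortality included, will be identified over one and two years. The Discussion expects an index that sorts patients into three risk bands for each outcome, again naming mortality.

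Two further points bear on the number of deaths. The Follow-up section reports assured funding for at least two years. The Population section rules out patients whom the GP expects to live 12 months or less ("Exclusion criteria will be a life expectancy of" introduces this criterion).

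**The concern.** In linear regression every patient with an outcome value contributes information, so a ratio of patients to covariables is a sensible rough guide. In Cox or logistic regression with an uncommon outcome, the information comes mainly from the events. A ratio of patients to covariables then says little about whether the model can be estimated.

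The article states one patient-based rule for all its regressions and also commits to a mortality model. A reader would take 200 per population as adequate for that model too. If deaths are few relative to the candidate predictors, the choice of predictors is unstable and predicted risks tend to be too extreme unless the fit is restrained. These predictions are meant to reach GPs and patients as part of the pattern on which therapy is discussed.

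**Working it through.** **Inputs from the article**
- Candidate covariables: about 20 (Sample size).
- Factor: 10 per covariable, counted in patients (Sample size).
- Cohort size: at least 200 in each of two cohorts, so 400 pooled (Sample size; Study design).
- Assured follow-up: two years (Follow-up).

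**Assumptions, because the article gives no rates**
- Two-year mortality: 3–10%, with 30% as an extreme check.
- Exacerbation rate: 0.2–1.0 per patient-year.

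**Step 1: the plan's own figure.** 20 × 10 = 200 patients. This reproduces.

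**Step 2: the same factor counted in deaths.** Deaths needed = 20 × 10 = 200. Mortality needed = deaths needed / patients. No assumed rate enters.

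| Deaths per covariable | Deaths needed | One cohort (200) | Pooled (400) |
|---|---|---|---|
| 10 | 200 | 200/200 = 100% | 200/400 = 50% |
| 5 | 100 | 100/200 = 50% | 100/400 = 25% |

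**Step 3: deaths under assumed mortality.** Deaths = patients × risk; deaths per covariable = deaths / 20.

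| Assumed two-year mortality | Deaths in 200 | Per covariable | Deaths in 400 | Per covariable |
|---|---|---|---|---|
| 3% | 6 | 0.3 | 12 | 0.6 |
| 5% | 10 | 0.5 | 20 | 1.0 |
| 10% | 20 | 1.0 | 40 | 2.0 |
| 30% | 60 | 3.0 | 120 | 6.0 |

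At 3–10%, the plan's own factor of ten would allow 0–2 parameters from one cohort and 1–4 from the pooled data. Even the extreme check of 30%, pooled, gives 6 deaths per covariable.

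**Step 4: which row applies.** The validation route is left open in Statistical analysis – prediction model. Deriving in one country, or in half of each cohort, leaves about 200 patients for derivation; only the pooled route with bootstrap uses 400. Fractional polynomials, which the plan intends to explore for continuous predictors, can use more than one parameter per predictor, so 20 covariables may mean more than 20 parameters.

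**Step 5: exacerbations.** The planned model uses recurrent events, so repeat events count. Events per cohort = 200 patients × 2 years × rate.

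| Assumed rate per patient-year | Events in 200 | Per covariable |
|---|---|---|
| 0.2 | 80 | 4 |
| 0.5 | 200 | 10 |
| 1.0 | 400 | 20 |

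Correlation between a patient's own events lowers the effective information below these totals. Whether ten per covariable is reached depends on a rate that the article does not give.

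**The case against.** **Sizing on the primary outcome is normal.** The index is built for CRQ, five of the seven models are CRQ models, and the patient rule fits them. This stands, and it limits the point to a secondary outcome. It does not make the rule valid for mortality, and the section does not restrict its scope.

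**The plan has safeguards.** It favours parsimonious models, avoids univariable screening, considers backward elimination, shrinkage, lasso and the garotte, and foresees a bootstrap check of over-optimism. It leaves room for pooling, further cohorts and longer follow-up, and 200 is a minimum. All of this is fair. But several of these are only options and none is tied to a number of deaths. The plan itself admits that the full model from which the garotte starts might be too big to fit.

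**The 20 candidates may not all be meant for mortality.** The models are said to share some predictors, not necessarily all. However, the article gives one count for the regression analysis and no smaller one for mortality.

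**Ten per covariable is only a rule of thumb.** True, but it is the plan's own factor, and halving it does not change the conclusion at the assumed 3–10%. A short list or per-model limit could sit in an analysis plan that is not shown. The finding is therefore not that such a list is missing, but that the stated rule does not fit one of the models it appears to cover.

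**Stronger readings that the article does not support.** A reader might infer that the exacerbation model is also undersized. Counting only patients with at least one event would suggest so, but that discards the repeat events which the planned model uses; at an assumed 0.5 per patient-year the total already reaches 200 per cohort. A reader might also infer that the mortality predictions must be mostly noise. That presumes an unpenalised fit of all 20 candidates, which the plan does not commit to. Nor can the effect of the life-expectancy exclusion be sized: it should lower early deaths, but the article gives nothing to quantify it.

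**Conclusion.** The point holds for mortality. That 200 deaths would be needed, meaning all of one cohort or half of both, follows from the plan's own factor and candidate count without any outside rate. The expected deaths per covariable (0.3–1.0 in one cohort, 0.6–2.0 pooled) rest on the assumed 3–10% two-year mortality and should be replaced by the sponsor's own figure.

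The stated size remains consistent with its rule for the CRQ models. For exacerbations adequacy is undetermined: the assumed range gives 4–20 events per covariable before allowing for within-patient correlation.

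This should be fixed, but it does not threaten the primary objective.

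**What to change.** In Sample size and Statistical analysis – prediction model:

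1. State that the rule of ten patients per covariable applies to the CRQ models only.
2. State the expected number of deaths, with the source of the mortality rate and the follow-up period.
3. Limit the candidate parameters of the mortality model by the number of deaths in the data used for derivation, counting every fractional-polynomial term. Use a short list fixed in advance from variables already collected, together with the shrinkage methods already under consideration.
4. Say that if deaths are too few for this, mortality will be reported as exploratory and left out of the index.

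For exacerbations it is enough to state the expected event rate, so that readers can judge adequacy.

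The cost is wording and a narrower stated scope for the mortality model. No extra patients or measurements are needed, and the choice among validation routes stays open.

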### Data collection and quality control

We will implement a series of measures to ensure high data quality.

1. Site investigators will collect the data using standardized forms.

2. All data will be collected and entered into a single database in MS-Access at the Academic Medical Centre provided by the Department of Clinical Epidemiology, Biostatistics and Bio-informatics. All data will be double entered and checked by a compare procedure.

3. International investigator meetings will be held (at least) twice yearly for all staff involved in data collection to detect any divergence in data collection procedures. This involves site mutual visits whenever possible.

4. Local investigators meetings will be held monthly, or more frequently if needed, to discuss recruitment of patients and problems in conducting the study.

5. E-mail will serve as the first line of non-urgent communication between research team members.

6. In Switzerland, monthly reports will be prepared by the principal investigator and sent to all GPs to inform about the number of patients recruited and important issues concerning the conduction of the study.

## Discussion

Management of COPD is challenging due to the various treatment options and the heterogeneous character of the disease. The actual (as opposed to ideal) assessment and treatment choices today are quite similar for all COPD patients and are often based on too few disease characteristics. This often leads to undertreatment of patients with severe COPD and overtreatment of patients with mild COPD. An example of overtreatment is the widely prescribed inhaled corticosteroids in mild patients. Results from recent studies suggest that GPs may not have methods available to sufficiently consider severity of disease for treatment decisions [3-11].

In preventive cardiovascular care, treatment decisions are based on the cardiovascular risk profile of the individual patient in primary care. Based on the most important predictors, patients fall into a specific risk profile. These profiles are formally coupled with treatment effects and costs considerations. Based on these components, treatment recommendations may be made. We believe that this so called risk index-guided treatment for specific patient profiles may well be applicable to COPD too.

The aim of this study to develop and validate a practical COPD disease risk index for the primary care will individualise and improve COPD management. Assessment of disease severity should not focus solely on lung function. An increasing body of evidence shows that additional information should be ascertained that better reflects disease severity than lung function [2,12-15].

We expect that after this study, the disease risk index will be ready for use in primary care. It will divide COPD-patients into specific risk profiles (low, medium and high risk) for each of the outcomes; COPD-specific health-related quality of life (domain-specific), exacerbation risk and mortality. In a second step we will incorporate treatment advices into the model by using data mainly from pertinent RCTs and meta-analyses. Ways to incorporate treatment advices into the prediction model may be challenging and are currently being explored by our team. In the development process of the cardiovascular risk model, the relative risk (RR) was treated as constant across all risk profiles.

Thus a predicted risk of cardiovascular death within 10 years of 30% may be reduced by RR = 0.8 to 24% (absolute risk reduction = 6%) whereas the same RR reduces a 3% predicted risk to 2.4% (absolute risk reduction = 0.6%). Adding costs considerations may lead to a recommendation to treat the former, and not the latter patient. It is unclear whether in our study, examining COPD, we will have the luxury of finding convincing evidence of constancy of relative risks (or odds ratios) of different treatments. If not, we will have to develop more refined methods.

Using the risk score that we will develop, the management of COPD in primary care will improve. Treatment decisions will be tailored better to the needs of the individual patient, resulting in less unnecessary treatment prescriptions, less exacerbations and a better COPD-specific health-related quality of life. We also expect that COPD management will become more cost-effective.
